##### Statistical analysis plan

Aim 1: To determine the association between dyadic relationships and health outcomes. We will conduct a cross-sectional analysis of the baseline interviews, stratified by cognitive function, across the disease spectrum from normal to dementia, assessing multiple aspects of the relationship from the perspective of each member as well as a comprehensive set of psychosocial attributes. The initial analyses for this aim will be bivariate in nature, and although largely descriptive, the results of these analyses will inform us as to what variables will be important to consider in more complex models in determining what relationship characteristic contribute to the health of individuals, both for the caregiver and PWD, across the normal-AD spectrum both cross-sectionally and longitudinally. These variables will be compared in predicting groups using multinomial logistic regression. In the case where variables are too highly correlated to be included in models together, strategies will be developed to choose the most important variables, either a priori or according to statistical criterion such as R-squares or standardized estimate comparisons, or to run multiple analyses with different sub-sets of variables.

Aim 2: To evaluate the change in the couple’s relationship, the potential causative factors that contribute to change in relationship characteristics, and the implications this change holds for the wellbeing of each member of the couple. Parameterization of repeated measures models [44]. The same fundamental procedures will be used for fitting all repeated measures models in this proposal. Because respondents will not be randomized, there may be differences across groups at baseline (e.g., age, education, relationship style). Therefore, we will include baseline measures in the trajectory analysis. Time will be treated as linear, but quadratic terms may be included if such a trend is graphically suggested. Correlation structures will be fit as autoregressive, generally the most appropriate for repeated measures data. Distributions of dependent variables will be either normal with an identity link or binary with a logit link. Models will be fit in SAS PROC GENMOD or PROC MIXED. For this aim, models will include a group by time interaction and will adjust for baseline variables. The model will be reduced in a backwards elimination fashion, removing variables that are non-significant and not important confounders. A significant interaction term in the final model will imply a significant difference in trajectories between groups, in which case adjusted mean and rates of changes will be presented separately for each time point. Post hoc analyses may involve testing pairwise comparisons across disease severity at specific time points or testing hypotheses around specific types of trajectories based upon observation of the adjusted least-square means or predicted probabilities by severity and time. Any post hoc analyses would be considered exploratory and p-values would be adjusted for multiple comparisons.

Longitudinal data will allow us to determine what relationship variables remain relatively static or are dynamic throughout the study and disease progression. This information will provide insight into what relationship characteristics may be responsive to psychosocial interventions. In addition, observing changes over time, via time-varying predictors and outcomes, will provide a closer approximation of causal inference; baseline severity along with changes in the relationship may be predictive of outcomes.

Aim 3: To use qualitative data collection and analysis to further explore the dynamic nature of the relationship characteristics of interest and enhance the interpretation of the results of the quantitative analyses. While the focus group interview guide will be heavily informed by the findings of the quantitative data, the analysis of the focus group data will be conducted according to the principles of framework analysis, which provides a systematic and transparent approach to qualitative research and can be applied deductively to answer a priori research questions and inductively to identify themes, insights or constructs. Framework analysis [45] includes five stages: familiarization; identifying a thematic framework; indexing; charting; mapping and interpretation. This analysis involves the identification and clustering of common themes in the data which will be carried out independently by two researchers. The researchers then will work together to reach a concordance of views on common themes. This independent analysis will be conducted by two trained qualitative researchers using NVivo software. As needed, a third qualitative researcher will be involved to resolve situations where concordance of themes cannot be reached.

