## Background

As the population continues to age, there is a corresponding increase in the number of people with Alzheimer’s disease and related dementias (ADRD) [1, 2] and the number of family caregivers. While funding for the development of novel pharmacological and disease-modifying targets often takes center stage [3, 4], to date, none has been identified that can substantially modify the disease course. Meanwhile, the financial and emotional cost to patients and families and the cost to the federal health care budget continue to grow.

Psychosocial interventions have substantial evidence of efficacy in improving outcomes for caregivers and persons with dementia (PWD) (e.g., the NYU Caregiver Intervention (NYUCI) [5–8]. The health outcomes demonstrated by the NYUCI are largely mediated by social support [9]; Moreover, many large-scale epidemiologic studies corroborate this finding and demonstrate that social support can predict better health outcomes and reduce the risk for premature mortality [10].

Partner relationships may be a particularly important form of social support, which is why the current study focuses on relationship characteristics of couples. In facing a chronic illness, both partners need support, and each is generally the primary support of the other [11]. Spouses frequently share stressors appraising them as “ours” rather than “mine”, pool resources, and actively engage in joint coping efforts [12]. Cross-sectional and longitudinal studies have documented concordance in levels and changes in spouses’ mental health and wellbeing. For example, in a longitudinal analysis of a repeated household survey, one partner’s mental health status predicted about 25% of the variance in the other partner’s mental health [13]. Older adults, whose relationships are generally of greater duration, were likely to have a higher concordance, which may reflect dynamic processes and shared experiences that increase with the length of the marriage [14]. The burden of dementia on older couples is especially poignant, and although they generally endure the illness together, cognitive decline and behavioral symptoms alter the role of the partner-caregiver and impact their relationship in ways this study aims to elucidate.

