##### Sample size calculation

Sample size was based upon the proposed longitudinal analysis investigating the effect of clinical group and relationship characteristics on changes in the primary outcomes over time. With an initial sample size of 300 couples (600 individual participants) and a potential dropout rate of 20% per group, we have powered the analysis to provide useful outcomes with a sample size of 240 dyads [41]. We have calculated the necessary sample size to sufficiently power the analyses for the smallest clinically substantive effect on the outcomes using the Geriatric Depression Scale scores in each of our three groups (cognitively normal controls, MCI, and AD). We made the following assumptions: 1) the minimum detectable effect size is 0.20, 2) there is 1 baseline measurement and either 3 or 5 post-baseline measurements, 3) two-tailed alpha error is 0.05, 4) power was set 0.8, and 5) the within-person association for over-time measurement is 0.7. With these assumptions, the study will need 50 patients for 3 follow-up measurements and 48 patients for 5 follow-up measurements per clinical group to adequately investigate the primary outcome, Geriatric Depression Scale scores [42]. The addition of covariates as well as multiple predictor variables and attrition will necessarily reduce this power; therefore, we have increased the sample size for those groups that may suffer most from attrition and offer the most clinical relevance (MCI and AD). Also, we will use model-building techniques (e.g., backward elimination) to fit the most parsimonious models. The use of sensitive and reliable measures and employing mixed-effects models to analyze repeated measures, which preserve all available data, will also, in general, improve power [43]. Lastly, the use of continuous predictor variables when available, e.g., MoCA score should also increase power over the use of categorical variables. With a sample of 300 couples at baseline, we are well powered to conduct the proposed analyses.

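### The repeated-measures models specify correlation over time within a person but none between partners, so standard errors will be wrong if both partners enter one model

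*Protocol article*

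**What the plan says.** The article's section Statistical analysis plan, under Aim 2, sets one covariance choice: "Correlation structures will be fit as autoregressive", with the reason that this usually suits serial measurements. Its scope is general: "The same fundamental procedures will be used for fitting all repeated measures models in this proposal". The software follows: "Models will be fit in SAS PROC GENMOD or PROC MIXED". For Aim 2 the "models will include a group by time interaction and will adjust for baseline variables", and a significant interaction is to be read as a difference in trajectories between groups. The aim covers both partners: "the implications this change holds for the wellbeing of each member of the couple".

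The section Sample size calculation begins "With an initial sample size of 300 couples (600 individual participants" and assumes a single correlation, 0.7 between repeated measurements on the same person. It also mentions mixed-effects models, but as a way to handle repeated measures and keep all available data. Nowhere does the article name a couple random effect, a partner covariance, or the dyad as the clustering unit.

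The Background reports that spouses are concordant in both levels and changes of mental health and wellbeing. It cites a household survey in which one partner's "mental health status predicted about 25% of the variance in the other" partner's mental health, and adds that concordance is likely higher in older adults.

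**The concern.** The only reason given for the autoregressive structure is that measurements are repeated over time. Partner correlation is a second source of dependence, which the document itself describes, and the specified structure does not represent it. With the person as subject, partners are treated as independent. With the couple as subject, a plain autoregressive structure would string two people's visits into one series, which is not how partners are correlated either.

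What is at stake is the validity of the Aim 2 inference when partners are pooled. The group-by-time test decides whether trajectories are declared different. Significance also drives the backward elimination, so wrong standard errors affect which predictors remain as well as the reported intervals.

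**Working it through.** **Inputs from the article**
- Enrolment groups: 60 normal, 140 MCI and 100 ADRD dyads (Overview).
- Dropout 20% per group; within-person correlation 0.7; two-sided alpha 0.05; power 0.80; 50 patients per group with 3 follow-ups or 48 with 5 (Sample size calculation).
- Partner association: about 25% of variance, from an external survey (Background). If this is a simple squared correlation, r = √0.25 = 0.5.

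**Assumption.** r is the residual correlation between partners on the quantity being tested. The article gives no value for this cohort, so a range is shown.

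**The plan's own figure.** The usual formula for the mean of m follow-ups is n per group = 2(1.96 + 0.842)²/d² × [1 + (m − 1)0.7]/m. With d = 0.20 it gives 314 (m = 3) and 299 (m = 5), not 50 and 48. Other standard variants that were tried with 0.20 did not give the pair either. It does appear at d = 0.5 (50.2 and 47.7). That is a separate matter; 50 and 48 are used below only as the stated targets.

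**Predictor shared by both partners.** The variance of a mean over pairs is multiplied by 1 + r. A model that ignores r therefore has standard errors too small by the factor 1/√(1 + r), and the true size of a nominal 5% test is 2[1 − Φ(1.96/√(1 + r))].

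| r | 1 + r | Model SE / true SE | True size, formula | True size, simulation | Simulation with partner correlation modelled |
|---|---|---|---|---|---|
| 0.10 | 1.10 | 0.953 | 6.2% | 6.1% | 4.9% |
| 0.25 | 1.25 | 0.894 | 8.0% | 7.9% | 4.9% |
| 0.50 | 1.50 | 0.816 | 11.0% | 11.0% | 5.0% |

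The simulation tested the group-by-slope difference with 60 against 100 dyads, 7 visits, autoregressive correlation 0.7 within person, partner correlation r and 20,000 replicates.

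**Condition for the group-by-time test.** The table applies to that test only if r describes the partners' changes. If partners resemble each other only through a constant couple-level shift, the shift cancels from each person's slope and does not inflate the test.

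**Predictor that differs within the couple.** If c is the correlation of the predictor between partners, the variance factor is roughly 1 + r·c. It is 1 + r when c = 1, 1 when c = 0 and 1 − r when c = −1. In the last case, with r = 0.5, the model's standard error is too large by 1/√0.5 = 1.41 and the nominal 5% test runs at about 0.6%.

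**Number of dyads.** At r = 0.5 with both partners contributing, 50 × 1.5 = 75 individuals, or 38 dyads; 48 × 1.5 = 72 individuals, or 36 dyads. The smallest group keeps 60 × 0.8 = 48 dyads.

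**The case against.** The strongest reply is that the clustering unit is unstated rather than wrong. The article does not say that both partners enter one model. Models fitted separately by role would keep the type I error intact, both SAS procedures can handle couples, and such syntax is often left to a fuller document. This limits the point but does not remove it. The text does not defer the covariance: it selects a structure, justifies it by repeated measurement alone and applies it to every repeated-measures model. No separation by role is described, and the 60 normal couples have no impaired partner and caregiver by which to separate them.

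A second reply is that group may not be shared by the couple. Enrolment strata are dyads, but the Overview also classifies participants at each visit from the MoCA and FAQ. On that reading, partners differ in group at enrolment in 140 + 100 = 240 of 300 couples. MoCA score, the continuous predictor favoured in the sample size section, also varies within couples. This stands: the inflation in the table belongs to predictors common to both partners.

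A third reply is that the 25% is not this study's residual correlation. It comes from a cited household survey, and nothing gives its size after adjustment or for changes. This also stands. The Background asserts concordance in changes as well as levels, so zero is not the natural default, but the size is unknown.

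Some stronger readings are tempting. A reader might infer that 600 people are counted as 600 independent units, but no calculation uses the 600. A reader might infer that separate models could not examine whether one partner's rating affects the other's outcome. They can, by entering both ratings as predictors; only a formal comparison of effects between partners needs a joint model. Nor does the article specify a partner-versus-partner contrast, so the 0.6% above only shows the direction of the error.

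**Conclusion.** The point holds in a conditional form. The article fixes a within-person correlation for all repeated-measures models and provides none between partners, while making both partners' outcomes the object of study and reporting that spouses are correlated. If partners are pooled, standard errors are wrong. For couple-level predictors they are about 5%, 11% and 18% too small at r = 0.1, 0.25 and 0.5, with true test sizes of about 6%, 8% and 11%. These figures rest on three assumptions: both partners in one model, a predictor common to the couple, and a partner correlation of that size in the quantity tested (for group by time, in changes). The documents do not support stating 11% as the study's error rate.

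The documents also do not support the inference that this defect makes the sample too small: at r = 0.5 the stated targets become 38 or 36 dyads, against 48 remaining in the smallest group. The fault concerns the validity of standard errors and p-values.

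**What to change.** In the Aim 2 text, state whether the two partners are analysed together, and name the dyad as the independent unit. Model partner correlation together with the autoregressive structure:
- PROC MIXED: SUBJECT=dyad with a person-by-time covariance such as TYPE=UN@AR(1), or correlated partner random effects. If random effects are used, include slopes as well as intercepts, because the key test concerns change. Treat partners as exchangeable in the normal couples.
- PROC GENMOD: SUBJECT=dyad with empirical standard errors.

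State also whether group is the couple's enrolment stratum or each person's classification at the visit, since this decides the direction of the bias. Where an effect of one partner's relationship rating on the other's outcome is to be claimed, enter own and partner ratings together. A full actor-partner model is an optional extension.

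The change is to wording and model statements; no new data are needed. The cost is somewhat wider confidence intervals for couple-level effects and a slightly more complex model.

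### The plan fixes an autoregressive correlation for every repeated-measures model with no check or robust standard error, which fits poorly with the 0.7 used for sample size and could weaken the Aim 2 group-by-time test

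*Protocol article*

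**What the plan says.** In the Statistical analysis plan, Aim 2, one set of procedures is laid down for all repeated-measures models. On the covariance it says: "Correlation structures will be fit as autoregressive, generally the most appropriate for repeated measures data". Either PROC GENMOD or PROC MIXED may be used, time enters linearly, and the group-by-time interaction decides whether trajectories differ. The section names no other structure, no comparison of fit, no random effect and no type of SE.

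The Sample size calculation section assumes that "the within-person association for over-time measurement is 0.7" and that "the minimum detectable effect size is 0.20". It takes "there is 1 baseline measurement and either 3 or 5 post-baseline measurements" and concludes that "the study will need 50 patients for 3 follow-up measurements and 48 patients for 5 follow-up measurements per clinical group". It also speaks of "employing mixed-effects models to analyze repeated measures, which preserve all available data", without saying which effects are random. The Methods overview schedules visits every 6 months for 3 years after baseline, which makes seven measurements.

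**The concern.** An AR(1) structure makes the correlation between two visits shrink geometrically with the gap. Starting from 0.7 between adjacent visits, baseline and month 36 would correlate at 0.7^6 = 0.12. Depression and relationship scores usually carry a lasting between-person component. If so, the correlation levels off above zero and AR(1) alone cannot describe it. With model-based SEs the fitted structure enters the error bars directly. An analysis that wrongly lets the correlation decay treats each person's visits as noisier about their own line than they are, which inflates the slope SE. It also treats distant visits as nearly independent, which shrinks the SE of a mean over visits. The group-by-time interaction is a slope contrast, so the test that carries Aim 2 is the one that loses power.

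**Working it through.** **1. Which correlation lies behind 50 and 48?** Inputs from the Sample size calculation: "two-tailed alpha error is 0.05", "power was set 0.8", correlation 0.7, and 3 or 5 post-baseline measurements. For a comparison of means over m visits,

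n per group = 2(1.960 + 0.842)² × VIF / d² = 15.70 × VIF / d².

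VIF, the variance of the mean relative to one visit, is (1 + (m − 1)0.7)/m under constant correlation: 0.800 for m = 3 and 0.760 for m = 5. Under AR(1) it is the average of all entries of the correlation matrix: 0.753 and 0.616.

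| Effect | Constant 0.7, m = 3 / 5 | AR(1) 0.7, m = 3 / 5 |
|---|---|---|
| d = 0.20, as stated | 314 / 298 | 296 / 242 |
| d = 0.50, assumed | 50.2 / 47.7 | 47.3 / 38.7 |
| Plan | 50 / 48 | 50 / 48 |

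The stated 0.20, read as a standardised difference, does not reproduce the plan's figures. With d = 0.5, constant correlation does and AR(1) does not. The relative fall from 50 to 48 (4%) does not depend on d. It is 5% under constant correlation (0.760/0.800) and 18% under AR(1) (0.616/0.753).

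**2. What happens if the truth is constant 0.7 and AR(1) is fitted?** Let V be the true covariance, W the inverse of the best-fitting AR(1) matrix (by likelihood, φ = 0.70, variance 1.0), and X the intercept and linear time. The model-based variance is (X′WX)⁻¹. The true variance is (X′WX)⁻¹X′WVWX(X′WX)⁻¹. The optimal variance is (X′V⁻¹X)⁻¹. Let k be model-based SE over true SE, and e be optimal over true variance. For an effect with 80% power under the correct model,

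power = P[Z > 1.96k − 2.802√e].

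With seven visits k = 1.853 and e = 0.757, so the threshold is 3.632 − 2.438 = 1.194 and power is 11.6%. With empirical SEs k is replaced by 1, the threshold is −0.478 and power is 68%.

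| Visits | Slope SE ratio | Slope type I error | Power, model-based | Power, empirical | Mean-level SE ratio | Mean-level type I error |
|---|---|---|---|---|---|---|
| 4 | 1.50 | 0.33% | 40% | 77% | 0.91 | 7.6% |
| 6 | 1.76 | 0.06% | 17% | 71% | 0.83 | 10.3% |
| 7 | 1.85 | 0.03% | 12% | 68% | 0.80 | 11.7% |

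A simulation of the 2-df group-by-time test agreed. It used seven visits, 48/112/80 per group (80% of 60/140/100), total changes of 0/0.2/0.4 SD and 1,500 runs. Power was 91% with constant correlation fitted, 12% with AR(1) and model-based SEs, and 84% with AR(1) and robust SEs.

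**3. Less extreme cases.**

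- *Baseline outcome as a covariate.* The remaining correlation is (0.7 − 0.49)/(1 − 0.49) = 0.41. Model-based power with 3, 5 and 6 follow-ups is 68%, 51% and 46%. Empirical power is 80%, 78% and 77%.
- *Mixed truths, seven visits, model-based SEs.* The variance shares are assumptions; the plan gives none.

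| Random intercept / AR / noise | AR parameter | Slope SE ratio | Power |
|---|---|---|---|
| 0.5 / 0.3 / 0.2 | 0.7 | 1.41 | 48% |
| 0.4 / 0.4 / 0.2 | 0.7 | 1.31 | 57% |
| 0.3 / 0.5 / 0.2 | 0.7 | 1.23 | 64% |
| 0.2 / 0.8 / 0 | 0.6 | 1.09 | 74% |
| 0 / 1 / 0 (AR(1) true) | 0.7 | 1.00 | 80% |

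**The case against.** A reader might infer that the plan contradicts itself. The text does not go that far. It never calls 0.7 constant or exchangeable, and 0.7 could describe adjacent visits. The evidence for a constant value comes from the pattern of 50 and 48, and it needs an effect size the plan does not state. Reading 0.20 as Cohen's f for three groups (largest pairwise difference 0.20 × √6 = 0.49) with 4 and 6 measurements gives 50.7 and 49.1 under constant correlation, which is near but not exact. This objection stands, so the inconsistency is inferred.

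A reader might also infer that the Aim 2 test is bound to fail. That needs AR(1) as the only covariance component together with model-based SEs, and the text fixes neither. GENMOD is allowed, and run as GEE with empirical SEs it gives valid SEs. The mixed-effects models named in the sample size section could include a random intercept. With an AR(1) residual, that model contains constant correlation as a special case and the loss disappears. Random effects and SE type are often left to a fuller plan. This also stands, and it limits the size of the concern. It does not remove it: the article states the structure for every model, justifies it only by a general claim, and equally allows PROC MIXED, whose default SEs are model-based.

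Finally, wrong SEs might suggest false claims of diverging trajectories. For slopes the error is conservative. Excess false positives concern group differences in mean level, not the interaction. The documents give no longitudinal correlations, so rapid decay cannot be excluded.

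**Conclusion.** The point holds as a weakness in a stated analysis rule. An autoregressive structure is chosen in advance for all longitudinal models with no safeguard, and it fits poorly with the correlation that best explains the sample size. For a contrast with 80% power under the correct model, the cost ranges from none (AR(1) true, or a random intercept fitted with it), through about 48% to 74% power (the mixed truths shown) and 46% to 68% (baseline outcome as covariate, 3 to 6 follow-ups), to 12% (constant 0.7, seven visits). All the reduced figures assume AR(1) alone with model-based SEs. With empirical SEs under constant 0.7, power is about 68% to 77% for seven to four visits. Under constant 0.7 with model-based SEs, mean-level group comparisons would reject at about 8% to 12% instead of 5%. The 12% is the worst case examined, not a forecast.

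**What to change.** Replace the sentence on correlation structure with a prespecified rule. One option is a random intercept and, where supported, a random slope, adding an AR(1) residual only if it improves fit by a named criterion. The other is an unstructured covariance with Kenward-Roger degrees of freedom. For models fitted by GEE, state that empirical (sandwich) SEs are reported. In the Sample size calculation, say whether 0.7 is constant or applies to adjacent visits, and use the same structure there as in the analysis. The cost is a few more covariance parameters, possible convergence checks, and a change of wording and model code. It should be done before any outcome model is run.

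### Aim 2 group trajectories are presented on condition of a significant group-by-time term that backward elimination does not protect, and no reporting is fixed for a non-significant result

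*Protocol article*

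**What the plan says.** The Aim 2 part of the section "Statistical analysis plan" in the protocol article sets out a sequence.

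- Starting model: "models will include a group by time interaction and will adjust for baseline variables".
- Reduction: "The model will be reduced in a backwards elimination fashion, removing variables that are non-significant and not important confounders". The group-by-time term is named neither as forced in nor as removable.
- Interpretation: "A significant interaction term in the final model will imply a significant difference in trajectories between groups".
- Presentation, joined to that sentence as its consequence: "in which case adjusted mean and rates of changes will be presented separately for each time point".

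The section does not say what is presented when the interaction is not significant. It says that the same fitting procedure serves all repeated-measures models, so the rule is not confined to one outcome. The sample size section adds that backward elimination is meant to give the most parsimonious models.

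**The concern.** How trajectories differ between cognitively normal, MCI and ADRD couples is the central quantitative result of Aim 2. The one stated route to group-specific means and rates of change runs through a significance test, after an elimination step that does not protect the tested term. Group by time is the hypothesis, so the exemption for important confounders does not clearly cover it.

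Two consequences follow if the rule is applied literally.

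1. After a non-significant test, the interaction may be removed. The final model then gives all groups one slope, and the reader gets no interval showing which differences were not excluded. Absence of significance can pass for equality of trajectories.
2. After a significant test, the differences shown have been selected for being large. With low power, their average overstates the true difference.

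**Working it through.** **Plan's own figures.** The article gives no power for the interaction test. Its nearest figures are 50 and 48 patients per clinical group (3 and 5 follow-ups) for an effect of 0.20, correlation 0.7, two-sided alpha 0.05 and power 0.8. The metric of the 0.20 is not stated. Read as a standardised difference in time-averaged means,

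n per group = 2(1.960 + 0.842)² × [(1 + (m − 1)0.7)/m] / d²,

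d = 0.20 gives 314 (m = 3) and 298 (m = 5), while d = 0.50 gives 50.2 and 47.7. The stated numbers therefore fit 0.50, not 0.20, on this formula. That mismatch is a separate matter. Here it is only the reason to show both effect sizes.

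**Inputs from the article.**
- 60/140/100 dyads (Overview) less 20% dropout per group (Sample size calculation): 48/112/80, total 240.
- Baseline plus six-monthly interviews for 3 years: 7 visits.
- Within-person correlation 0.7; two-sided alpha 0.05; autoregressive correlation structure.

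**Assumptions not in the article.** Complete data in 240 dyads, one analysed member per dyad, known variance, linear true change of 0, d/2 and d SD over 3 years in normal, MCI and ADRD, and 0.7 taken either as constant or as the correlation between adjacent visits.

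**Slope variance per person** (time scaled 0 to 1 over 3 years, centred values c = −1/2, −1/3, …, 1/2).
- Constant correlation: (1 − 0.7)/Σc² = 0.3/0.778 = 0.386.
- First-order autoregressive: 1/[c₁² + Σ(cⱼ₊₁ − 0.7cⱼ)²/(1 − 0.7²)] = 1/[0.25 + 0.1642/0.51] = 1/0.572 = 1.749.

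**Power of the 2-df interaction test at d = 0.20.** The weighted mean slope is (112 × 0.1 + 80 × 0.2)/240 = 0.1133. The weighted sum of squares about it is 48(0.1133)² + 112(0.0133)² + 80(0.0867)² = 1.237. The non-centrality is 1.237/0.386 = 3.21 (constant) or 1.237/1.749 = 0.71 (autoregressive). Against the 5% chi-square limit of 5.99, power is 34% or 11%. At d = 0.50 the sum of squares is 1.237 × 6.25 = 7.73, and power is 98.5% or 45%.

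**Mean ADRD-normal difference among significant results** (simulation of the three slopes with these variances):

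| True difference | Correlation | Interaction significant | Mean difference if significant | Ratio to truth |
|---|---|---|---|---|
| 0.20 SD | constant | 34% | 0.31 | 1.56 |
| 0.20 SD | autoregressive | 11% | 0.52 | 2.60 |
| 0.50 SD | constant | 98.5% | 0.50 | 1.01 |
| 0.50 SD | autoregressive | 45% | 0.70 | 1.39 |

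Without the filter, the mean estimate equals the true value in every row.

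**What an always-reported interval would show.** The standard error of the ADRD-normal difference is √[V(1/48 + 1/80)], which is 0.113 or 0.241. The 95% half-width is 1.96 times that: ±0.22 SD or ±0.47 SD. Under the planned autoregressive structure, a non-significant result would be compatible with differences well above 0.20 SD.

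**The case against.** The best defence is that the article is silent, not restrictive. It says what happens after a significant interaction; it does not say that nothing is shown otherwise. A reader might infer that group trajectories appear only after significance and are otherwise dropped, but the text does not state this. Presenting results separately may simply mean separate rather than pooled presentation, with group main effects and a common slope still given. The article also allows post hoc work "based upon observation of the adjusted least-square means or predicted probabilities by severity and time", which is not expressly tied to significance. Removal of the interaction is likewise not stated: the confounder wording fits covariates best, and testing the term in the final model may presuppose that it is still there. All of this stands. What remains is that a presentation rule is written down, that it depends on the p-value, and that no sentence protects the interaction. The post hoc route is optional and exploratory ("Any post hoc analyses would be considered exploratory and p-values would be adjusted for multiple comparisons"), so it does not replace main reporting.

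A reader might also infer that the study must show either inflated differences or none. That is too absolute: the bias depends on power and nearly vanishes in the 98.5% row above.

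Finally, a reader might infer that a linear model cannot yield rates of change for each time point. The article blocks this: "Time will be treated as linear, but quadratic terms may be included if such a trend is graphically suggested". With a quadratic term the rate does vary over time. For example, take a group that falls 0.4 SD in year 1 and then stays flat. A straight line misses by 0.14 SD at baseline and at 12 months; a quadratic misses by at most 0.07 SD at any visit. Modelling visit as a seven-level factor would be a preference, not the correction of an error.

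**Conclusion.** The concern holds in a limited form. The plan makes presentation of adjusted group means and rates of change conditional on a significant group-by-time term, after an elimination that does not exempt that term, and it leaves the non-significant case open. At a true ADRD-normal difference of 0.20 SD, the presented difference would be overstated about 1.6-fold (constant correlation) to 2.6-fold (autoregressive), and the condition for presenting it would not be met in about 66% to 89% of studies. At 0.50 SD the overstatement is 1% or about 1.4-fold. The size rests on the assumptions listed, above all on reading 0.20 in SD units and on the ordered 0, d/2, d pattern. The direction does not: selecting on significance pushes the reported differences away from zero whenever power is limited. The documents do not show that group results will be withheld; they show a rule under which they could be.

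**What to change.** Add two sentences to the Aim 2 analysis text.

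1. The group-by-time term is exempt from backward elimination in the Aim 2 models that test it; elimination applies to the other covariates.
2. Each group's estimated 3-year change and the pairwise differences between groups are reported with 95% confidence intervals whatever the p-value of the interaction.

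The interaction test can stay as the formal test of differing trajectories. The cost is a few more table rows and a slightly less parsimonious model; no new data are needed.
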